**Methods and analysis:**

Participants are adolescents aged 12–18 with a visible difference and experiencing appearance-related distress. In this two-armed randomised controlled trial, 224 adolescents will be randomised to care as usual or YP Face IT. Adolescents will complete questionnaires at baseline, at 13 weeks and at 25 weeks. Primary outcomes are differences in social anxiety and body esteem between YP Face IT and care as usual. Secondary outcomes are differences in aspects of self-worth, perceived stigmatisation, health-related quality of life, life engagement, appearance-related distress and depressive symptoms between the two groups.

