### Study design

A flow chart of the RCT is depicted in figure 1. Prior to baseline, the inclusion and exclusion criteria as mentioned before (with the exception of appearance-related distress) are queried in a telephone call with the parent or adolescent. Appearance-related distress is measured based on the questionnaires completed at T1 (baseline). Adolescents will receive an email with a link to all questionnaires, with the exception of the CBSA. They will receive this questionnaire by post. This procedure is the same for T2 (13 weeks, direct follow-up) and T3 (25 weeks, 3-month follow-up).

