**Figure 1 F1:**
[figure not shown]
Flow chart of the study design. CAU, care as usual; YP, Young People.

After completing the questionnaires, screening for appearance-related distress will take place by the research team. The scores on the SAS-A, BESAA and CDI-2 are considered. For the SAS-A and the BESAA, adolescents that score 0.5–2.0 SD above average will be included in the study. For the CDI-2, we will include adolescents scoring in the 70th–90th percentile, as the manual states that this corresponds to subclinical symptoms of depression.^32^ Adolescents that score within the defined range for one or more of the questionnaires will be randomised into the study. Adolescents that score below this range will be excluded from participation. Adolescents that score above this range will be contacted by the research team to assess whether there are clinical psychological symptoms. A phone call is made to both the adolescent and one of his/her parents. During this phone call, the Diagnostic and Statistical Manual of Mental Disorders (DSM) criteria for depressive disorder, social anxiety disorder or another suspected diagnosis will be asked. If suspicions of clinical psychological symptoms arise, the adolescents are referred to the appropriate psychological care. If no clinical symptoms are present, the adolescent is randomised into the study.

Adolescents with subclinical symptoms will be randomised to either CAU or YP Face IT. Adolescents in the CAU group will receive CAU and will complete T2 at 13 weeks and T2 at 25 weeks. The CAU group will have the opportunity to complete YP Face IT after their participation in the study. Adolescents in the YP Face IT group will receive CAU and YP Face IT and will complete questionnaires immediately after completing YP Face IT (T2; 13 weeks) and 3 months after completing YP Face IT (T3; 25 weeks).

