### Statistical analysis

The data will be analysed using multilevel linear regression analyses. There will be two levels in the models. The participants constitute the upper level and their repeated measures the lower level. For each outcome variable, a model will be postulated using treatment group, time and interaction with treatment group as fixed effects. Time will be entered in two ways: categorical and continuous. First, for categorical, we will postulate a model with T2 (direct follow-up) and T3 (3-month follow-up) using T1 (baseline) as reference group. Second, for continuous, we will apply the logarithm of time, as generally treatments have the largest effect at start and the level of functioning stabilises on the long run. The deviance statistic using restricted maximum likelihood will be applied to determine the covariance structure. The deviance test will be used to determine whether the more parsimonious (log) model is a too rigorous oversimplification.^35^ Effect sizes will be calculated from dividing differences between the primary time point (ie, 3 months) estimations and baseline by the estimated baseline SD. Analyses are done on an intention-to-treat base.

Participants who do not experience subclinical symptoms at T1, and are thus not randomised, will not be included in the analyses.

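### The effect-size formula is a change from baseline with no between-arm term; read literally, it would include regression to the mean from screening at T1

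*Protocol article*

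**What the plan says.** The abstract of the protocol article frames the question between arms: "Primary outcomes are differences in social anxiety and body esteem between YP Face IT and care as usual". The Statistical analysis section fits a multilevel model that suits this question: "a model will be postulated using treatment group, time and interaction with treatment group as fixed effects", with T1 as the reference when time is categorical. It then defines the reported effect size: "Effect sizes will be calculated from dividing differences between the primary time point (ie, 3 months) estimations and baseline by the estimated baseline SD". The two terms subtracted are a time point and baseline, and neither arm is mentioned.

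The Study design section says that appearance-related distress is assessed from the questionnaires completed at T1, which is also the baseline. The text below Figure 1 sets the windows. For the two primary scales: "For the SAS-A and the BESAA, adolescents that score 0.5–2.0 SD above average will be included in the study". For depressive symptoms: "For the CDI-2, we will include adolescents scoring in the 70th–90th percentile". One scale is enough: "Adolescents that score within the defined range for one or more of the questionnaires will be randomised into the study". Adolescents above the range are telephoned and are randomised if no clinical symptoms are found. The analysis leaves out those who were screened but not randomised.

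**The concern.** A change from baseline within one arm answers a different question from the one the trial asks. In this trial the two can differ for a specific reason: both primary scales are used to select participants, and the scores that select them are also the baseline. A group chosen partly for elevated distress on one occasion will, on average, score somewhat closer to its population mean on the next, whatever is done in between. A within-arm figure counts that movement as if it were effect. It would also stand beside the planning value of d=0.50 and the d of 0.80 and 0.83 quoted from the adult study, and readers would compare them.

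The denominator raises a smaller point. The baseline SD comes from the screened sample and is probably narrower than the SD of unscreened adolescents. That is so whether the numerator is within or between arms.

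**Working it through.** **Planning figure.** Inputs from the Sample size section: power 0.80, two-sided alpha 0.025, r=0.70, three linearly decreasing measurements, d=0.50, 50% dropout. Take care as usual as flat and YP Face IT at 0, -0.25 and -0.50 SD, with equal correlations. The group-by-time F test (2 df) has noncentrality (n/2) × Σ(δ − mean δ)² / (1 − r). With n=56 per arm this is 28 × 0.125 / 0.30 = 11.67, and the power is 0.799; 57 per arm gives 0.807. Then 112 / (1 − 0.5) = 224. The stated sample size is therefore reproduced, with d=0.50 taken as a between-arm difference in change. Other forms tried give different numbers per arm: 77 (follow-up only), 46 (change score), 39 (ANCOVA) and 61 (mean of three measurements).

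**Regression to the mean within an arm.** For a scale in norm-SD units with population mean μ, unscreened retest correlation ρ, and screened-sample mean m and SD s at T1, the expected untreated change is (1 − ρ)(m − μ). Divided by s, it is the spurious within-arm effect size. The screening rule was simulated on three correlated normal scales to obtain m and s for the SAS-A.

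From the article: the windows, the one-or-more rule, and the admission of some above-range scorers. Assumed, because the article does not give them:
- correlation between scales 0.3 to 0.7;
- share of above-range scorers admitted 0 to 1, applied either to anyone above range on any scale or only to those in range on none;
- μ at the norm or 0.5 SD worse;
- ρ of 0.6 to 0.8 (the 0.70 in the Sample size section is not described as an unscreened retest value);
- the BESAA window taken in the direction of distress, as the Participants section implies.

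| Case | m | s | Calculation | Result |
|---|---|---|---|---|
| Lowest, ρ=0.70, μ=0 | 0.335 | 0.874 | 0.30 × 0.335 / 0.874 | 0.12 |
| Illustrative, ρ=0.70, μ=0 | 0.565 | 0.846 | 0.30 × 0.565 / 0.846 | 0.20 |
| Highest, ρ=0.70, μ=0 | 0.696 | 0.722 | 0.30 × 0.696 / 0.722 | 0.29 |
| Lowest overall (ρ=0.70, μ=0.5) | 0.534 | 0.814 | 0.30 × 0.034 / 0.814 | 0.01 |
| Highest overall (ρ=0.60, μ=0) | 0.707 | 0.738 | 0.40 × 0.707 / 0.738 | 0.38 |

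**Within against between arms.** The illustrative case has a between-scale correlation of 0.5 and half of the adolescents who are above range, and in range on no scale, admitted. Simulating two randomised arms gives, in baseline SDs of improvement:

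| True effect (norm SD) | YP Face IT, within | Care as usual, within | Between arms |
|---|---|---|---|
| 0 | 0.20 | 0.20 | about 0.00 |
| 0.50 | 0.79 | 0.20 | 0.59 |

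The literal formula would report 0.79 where the between-arm form of the same formula gives 0.59.

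**Denominator.** Over all runs s lies between about 0.64 and 0.94 of the unscreened SD. A true difference of 0.50 unscreened SD would then read as about 0.53 (0.50/0.94) to 0.79 (0.50/0.635, with s unrounded).

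**Time point.** The Statistical analysis section calls T3 the 3-month follow-up, and Study design places it at 25 weeks, 3 months after the programme ends. T2 at 13 weeks is also about 3 months, counted from baseline. The phrase in the effect-size sentence fits either.

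**The case against.** The strongest reply is that the sentence should be read with the model above it. The model contains the group-by-time interaction with T1 as reference, and the abstract states between-arm outcomes. Applied to the interaction term, change over baseline SD is a between-arm effect size, and randomisation removes regression to the mean. This stands as a possible reading, and the article does not exclude it. A reader might infer that an ineffective programme is bound to show a positive effect. The article does not support that: it holds only if the figure is reported within an arm, and care as usual would then show the same movement. The significance test is untouched in either case.

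A reader might also take the window at face value and compute a much larger bias. Full truncation of one scale to 0.5–2.0 SD gives mean 1.043 and SD 0.388, so 0.30 × 1.043 / 0.388 = 0.81. The one-or-more rule and the admission of some above-range scorers mean that the trial sample is not truncated in this way.

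The use of 0.70 is open to challenge too. If it describes the screened participants, the unscreened correlation is higher. With s=0.85, solving 0.49(1 − ρ²) = 0.51ρ²s² gives ρ of about 0.76. The spurious change is then about a fifth smaller (0.24 against 0.30 of m − μ). This stands, and is one reason to quote a range.

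Last, dividing by the baseline SD is an ordinary choice, and the Sample size section does not put d=0.50 in norm units. It therefore cannot be said that this denominator makes the result incomparable with the planning value. The alternatives have costs: a reference-SD window exists only for the SAS-A and BESAA, and the T3 SD can be altered by treatment and by the anticipated 50% dropout.

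**Conclusion.** The concern holds as a fault in how the reported effect size is defined. The formula is stated, it omits the between-arm term, and its literal result does not answer the trial's question. On that reading, an arm with no effect would show roughly 0.1 to 0.3 baseline SD of improvement, given an unscreened retest correlation of 0.70 and a population mean at the norm. Over the wider assumptions the range is 0.01 to 0.38, so the distortion could be negligible. That selection at T1 feeds regression to the mean into a within-arm figure follows from the design; its size rests on values that the article does not give. The narrower denominator calls for a statement in the report and does not invalidate the formula. The group-by-time test and the sample size do not depend on this sentence.

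**What to change.** Replace the sentence with a definition along these lines: *For each outcome, the effect size is the model-estimated difference between YP Face IT and care as usual in change from baseline to the primary time point (the group-by-time contrast), divided by the estimated baseline SD of the randomised sample, with a 95% CI. The difference on the raw scale is reported beside it.*

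Two additions are needed. Name the primary time point as T2 (13 weeks) or T3 (25 weeks, 3-month follow-up). State that the baseline SD comes from a sample screened on the same scores, so the standardised value may be somewhat larger than in unscreened units; with that statement it can remain the denominator. Within-arm changes should appear only descriptively, with a note that they include regression to the mean.

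This costs a few lines of text and changes nothing in design, data collection or testing. The downside is that the reported effect sizes will probably be smaller than under the literal formula.

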### Monitoring

As the risks associated with this study are minimal, monitoring will take place once a year. An independent investigator will randomly check study documents, participant selection and participant safety. As minimal risks are involved, no interim analyses will be done.

Auditing may be done by the Erasmus MC-Sophia Children’s Hospital.

### Patient and public involvement (PPI)

The original YP Face IT intervention was developed in collaboration with adolescents and the charity Changing Faces.^16^ For the Dutch translation, six adolescents and their parents have read and reviewed the translations. Prior to this RCT, an acceptability and feasibility study was conducted. In this study, 14 adolescents completed YP Face IT and participated in an interview. Feedback was asked on the intervention, as well as on the general study procedures (ie, information packages, questionnaires and contact with the research team). Patient associations will be invited to help develop our dissemination strategy.

### Trial status

The trial described in this paper has started in September 2019. Recruitment of participants will be until November 2020. Data collection will be until May 2021, after which the data will be analysed.

## Ethics and dissemination

### Ethics, consent and permission

This study will be conducted in accordance to the Declaration of Helsinki.

Research ethics approval was obtained from the medical ethics review committee in Rotterdam (reference number MEC-2018-052/NL63955.078.18). Any amendments to the study protocol and (serious) adverse events will be reported to this committee.

### Data management and confidentiality

To ensure anonymous processing of the data, every participant will receive a study number. All research data will be processed using only this study number. The handling of data will comply with the European General Data Protection Regulation. The study master file and all research data will be saved for 15 years, unless participants or their parents/guardians do not give consent for saving their data.

All data will be stored in locked cabinets or password-protected documents. The data, including the final dataset, can be accessed only by members of the research team.

### Dissemination of research findings

Results of this study will be presented on national and international conferences and in peer-reviewed scientific journals, within the scope of the target groups. The results will also be relayed to patients through patient organisations. Participants are also given the option to sign up for a brief study report after the results are finalised. If deemed effective, YP Face IT will be implemented in hospitals in the Netherlands.

## Discussion

The Dutch YP Face IT Study aims to test the Dutch version of YP Face IT. With this RCT, we aim to retrieve data on the effectiveness of the intervention.

### Strengths and limitations

A particular strength of this study is that it follows a stage model of behavioural therapies research^36^ and has excellent methodological quality. Previous research has lacked methodological rigour, due to small sample sizes, not including a control group or not blinding personnel or participants.^15^ Due to the nature of this study, blinding of participants is not possible. However, this study does include an adequate sample size and includes a control group and blinding of relevant personnel. With this methodological quality, we hope to be able to provide evidence base for YP Face IT and thus provide one of the first evidence-based treatments for adolescents with a visible difference.^15^ Furthermore, by recruiting our participants through several channels, we will be able to obtain a sample that is representative for Dutch adolescents in general rather than solely Rotterdam, where the research team is located. Because the intervention is available online, participants throughout the entire country are able to participate without adding extra burden to participating.

In addition to strengths, this study also has some limitations. First, the intervention is available for a range of conditions causing a visible difference. The overall group results might not be generalisable to one specific group. Second, participants are not blind to the treatment condition. Participants are informed about the randomisation groups. They are also informed that, if randomised to the CAU group, they will have the possibility to access YP Face IT after the study. This is a more ethical option than not offering treatment after the study, and this knowledge may help keep attrition low. However, waiting-list designs may lead to an overestimate of the treatment effect.^37^ Furthermore, this study includes only self-report measures. Diagnostic interviews or parent reports could provide more enriched data. However, due to time and financial constraints, these data will not be collected.
